## Methods

### Experimental design

We propose a pragmatic randomised controlled multicentre trial of the improved effectiveness of an integrated global care program (PEPCI for Parcours Environnement PériConceptionnel en Infertilité) in comparison with usual care (i.e., a parallel-arm superiority trial). Four centres in Paris and its suburb area with various socioeconomic contexts will participate. Use of a pragmatic approach and an effectiveness assessment will assume not only clinical efficacy but also feasibility issues such as acceptability of care by patients under usual conditions as reflected by wide selection criteria [56]. Thus, this trial will use the ‘cohort multiple randomised controlled trial’ methodology [57] to strengthen external validity by limiting the bias that may result from the period of initial consent to randomisation or from the deception of being allocated to the control group.

Moreover, this design allows us to keep all people under survey to obtain realistic estimates of noncompliance and effectiveness of the program. It reproduces ‘patient-centred’ informed consent, in that the process of obtaining patient information and consent aims to replicate the one used in real-world routine health care.

### Study recruitment

Recruitment for the study will follow a three-step process (Fig. 1) as follows:
In practice, at their first visit to the ART centre, all the attending couples will be invited to participate in an observational survey cohort for evaluation purposes to facilitate our access to their data that are prospectively collected through standardised forms.Unless a couple has refused to be included in the ‘whole’ cohort, they will be checked for eligibility as the consultation is going on and, if eligible, will be informed of such and asked for written consent for biological sample collection (biobank).In the case of biobank consent, an ‘on-the-fly’ randomisation will be performed by the physician on a dedicated website that selects PEPCI candidate couples who are offered the PEPCI experimental intervention (experimental group). Thus, the process of obtaining the couple’s information and consent replicates the real-world routine health care and concerns the intervention only and not the trial. Couples randomised in the experimental program can refuse the experimental program. In this case, they will benefit from usual care. Couples randomised in the usual care group (control group) won’t need to provide any additional information since they already agreed to the collection of data and biological samples for evaluation purposes. The randomisation sequence is prepared in advance and stratified by centre with unrevealed varying block sizes, while allocation will be programmed according to a 2:1 control:experimental ratio in line with the sample size calculation and to minimise global cost.

**Fig. 1 Fig1:**
[figure not shown]
Recruitment and composition of the PEPCI study

Analyses will be performed according to an intention-to-treat principle and will compare, among eligible and biobank-agreeing patients, all randomised to usual care (control arm) participants to all candidate PEPCI participants, depending on whether they have consented to the PEPCI intervention or not. The trial will be conducted and reported according to the Consolidated Standards of Reporting Trials guidelines and their pragmatic extension [58].

### Selection criteria

#### Whole cohort

Heterosexual infertile couples (lack of pregnancy after 12 months of unprotected intercourse), including men aged 18 to 60 years and women aged 18 to 43 years will be eligible for inclusion in the whole cohort. Other main inclusion criteria include a good understanding of the French language by both couple members and the approval of data collection by both parents-to-be.

#### Eligible patients for the controlled trial

After inclusion in the study cohort, both members of the couple must give their informed written consent for the collection of their biological samples. In addition, according to French laws, they must be affiliated with a social security scheme (beneficiary or legal). Lastly, they must have access to an Internet-connected device with a webcam at home. They must not present any contraindication to adapted physical activity.

The main exclusion criteria are (1) gamete donation; (2) BMI of more than 40 kg/m^2^ for a member of the couple, requiring mandatory care; (3) viral context (i.e., one or both members of the couple shows human immunodeficiency virus, hepatitis B, C infection); (4) inability to comply with the care program—notably, the physical exercise regimen; (5) ongoing pregnancy; (6) medically-treated diabetes mellitus; and (7) psychiatric pathologies requiring or currently under treatment.

The different groups are shown in Fig. 1.

### Data collection procedures and assays

#### Whole cohort

All patients included in the whole cohort (including the PEPCI study) will undergo a baseline evaluation of diet and lifestyle factors through the following questionnaires:
Dietary intake: ‘SUVIMAX questionnaire’ [59, 60] for 3 days, consecutive or not with a weekend day, including medication/dietary supplements use (multivitamins, folate) and binge-eating disorders (Binge-eating Scale) [61]Physical activity level: ‘International Physical Activity Questionnaire (IPAQ)’ [62, 63]Sleep quality: ‘Pittsburgh Sleep Quality Index (PSQI)’ [64, 65]Depression and anxiety troubles: ‘Hospital Anxiety and Depression (HAD) scale’ [66, 67]Quality of life: ‘Duke questionnaire’ [68]Locus of control and individual beliefs: French version of the C form of the Multidimensional Health Locus of Control [69] to understand factors of adherence to the program and pregnancy [52]

#### Patients involved in the controlled trial (Figs. 2 and 3)

All couples recruited in this trial will be assessed at baseline (M0), while the couples who accepted to undergo the PEPCI intervention will be evaluated 3 months later (M3). Then, all couples (control and experimental arms) will be followed for 12 months (M12) or evaluated at the time of pregnancy diagnosis and then until delivery.

**Fig. 2 Fig2:**
[figure not shown]
Progress of care during the PEPCI study. Green: control group; blue: experimental group

**Fig. 3 Fig3:**
[figure not shown]
PEPCI study visits schedule

#### Data collection and assays at baseline (M0)

In both arms, blood (after a 12-h fasting period) and sperm will be collected for immediate and further analyses (biobank). Immediate analyses include (1) metabolic assays: measurement of total plasma cholesterol, high-density lipoprotein cholesterol (HDL), low-density lipoprotein cholesterol (LDL), triglycerides, and plasma glucose concentrations; (2) one-carbon metabolism assays: measurement of folate, homocysteine, and vitamins B6 and B12; and (3) sperm parameters assessment. Semen samples will be collected by masturbation in a sterile plastic cup after three to 5 days of sexual abstinence. After semen liquefaction, conventional sperm parameters (volume, concentration, and mobility) will be evaluated according to World Health Organization guidelines [70]. Sperm DNA integrity will be assessed with the terminal deoxynucleotidyl transferase dUTP nick-end labelling assay [12] and flow cytometry.

For the members of couples who agreed to receive the intervention only, a detailed multidimensional evaluation will be performed to determine the content of the tailored intervention. Three caregivers, i.e., a sports physician, a dietician, and a psychiatrist, will see in turn and separately each member of the couple during the same half-day, with procedures as follows:
The sports physician will perform an interrogation (e.g., a familial history of obesity, diabetes, or cardiovascular diseases and personal history of metabolic, endocrinologic, and cardiovascular diseases); a physical examination (i.e., blood pressure, heart rate, BMI, and waist and hip circumferences); a cardiovascular (rest electrocardiogram), rheumatologic, and endocrinologic examination if needed; and a body composition assessment (single-frequency bioelectrical impedance analysis at 50 kHz using the Tanita BC 420 S MA from Tanita Corp., Tokyo, Japan) [71]. The physician also will evaluate physical activity levels through the self-assessed IPAQ questionnaire filled upstream on the web platform.The dietician will evaluate diet and eating habits, individual tastes, and abilities. Interrogation is partly based on the results of the Binge eating Scale and a self-reported food frequency questionnaire filled on the web platform. The dietician verifies the responses to the food frequency questionnaire with the patients (e.g., for declared quantities).The psychiatrist will screen the participants for depression and anxiety using the self-reported HAD questionnaire. Both members of the couple will undergo a structured clinical interview based on (1) the Miniature International Neuropsychiatric Interview (MINI 5.0) [72] for the diagnosis of psychiatric conditions according to the *Diagnostic and Statistical Manual of Mental Disorders*, fourth edition and (2) on the Alcohol, Smoking and Substance Involvement Screening Test for the screening of substance use disorders.

#### Data collection and assays 3 months after M0 in the intervention group (M3)

Couples included and who have consented to the initial PEPCI intervention (experimental arm) will complete a second consultation with the same sports physician, dietician, and psychiatrist, undergoing the same evaluations as included in M0 (i.e., questionnaires and sample collections).

#### Data collection and assays 12 months after the inclusion or when pregnancy is diagnosed (M12)

Both arms (experimental and control) will be assessed at 12 months from inclusion or sooner in case of pregnancy (when clinical pregnancy is diagnosed, after 6 weeks of amenorrhea) for the following reasons:
Evaluation of the periconceptional environment through the same self-questionnaires, blood and sperm collection, and anthropometric parameters (biomarkers and biobank) as described aboveCollection of interventions in ART

#### Data collection in the case of pregnancy

The centre coordinators (a physician specialist in reproductive biology and an endocrinologist) will collect data concerning the evolution of the pregnancy until birth.

### Interventions

#### Lifestyle interventions (Fig. 4)

Couples included in the control group will benefit from usual care after the M0 visit. A booklet about a French national nutrition and health program (Programme National Nutrition Santé; PNNS) dedicated to pregnancy will be given to the couple.

**Fig. 4 Fig4:**
[figure not shown]
PEPCI intervention program: Experimental group

For the couples accepting the PEPCI intervention (experimental group), a multidisciplinary staff meeting will be organised at the end of the M0 visit. The dietician, endocrinologist, sports physician, psychiatrist, and physician specialist in ART will, together, establish a baseline periconceptional profile from all the M0 assessments to determine two to three individual objectives to be negotiated with both members of the couple. Indeed, the key point is to allocate specific and relevant proposals to each patient from among the following:
Diet: If required, a personalised diet prescription according to the personal assessments will be designed with personalised follow-up conducted during the following 3 months through a web platform. Overweight or obese patients will be suggested to enter into a three-month supervised program through a web platform with the possibility to ‘virtually consult’ the dietician up to once a week. The French dietary guidelines (PNNS) can be adapted according to the tastes of the patient, with the a priori objective to lose 1 kg per month [73]. Excessive weight loss in a short period of time has been reported to have a negative effect on the outcome of ART [74] and to be associated with an increased risk of adverse pregnancy outcomes such as low birth weight or miscarriage [75]. In addition, qualitative changes in diet are suggested independently of BMI status. According to the PNNS program, a healthy diet is recommended but the dietician can recommend the patient to change their diet to a Mediterranean one [30, 76]. Finally, the prescription of folic acid (0.4 mg a day) will be systematically checked.Physical activity: A personalised physical activity program individualised to the patients’ physical fitness, preferences, and possibilities will be proposed. Exercise sessions are scheduled online with a certified adapted physical activity trainer via the web platform for 30 min, twice a week. Patient fitness data will be assessed online at M0 and M3 by the trainer, including aerobic fitness with the two-minute step test, a perceived exertion rating using the modified Borg scale [77], submaximal isometric femoral quadriceps strength with the Killy test, abdominal endurance with the curl-up test [78], flexibility of the whole spine and pelvis with the fingertip-to-floor test [79], and unipodal balance with eyes open and closed with the Flamingo test [80]. Adherence to planned sessions will be assessed via the web platform.Psychologic care and addiction: A follow-up with the psychologist will be systematically offered for couples or individuals depending on the wishes of the participants and their needs as assessed by the psychiatrist. The follow-up will consist of three to eight sessions (duration of 45 min) over the 3 months of the intervention. In cases of a psychiatric diagnosis requiring specialised care, patients will be referred to a psychiatrist and not included in the study. If required, a follow-up by a nurse specialised in addiction treatment will be offered. The follow-up consists of three to five sessions (duration of 30 min) of phone counselling over the 3 months of the intervention.

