### Sample size and statistical analysis

We have considered (1) that the PEPCI intervention would lead to a relative risk of clinical pregnancy of 1.6 [28] as compared with usual care (i.e., from 20 to 32% in absolute values, respectively) and (2) that refusal of PEPCI experimental care would intervene for 20% of subjects. The resulting difference, according to the intention-to-treat principle, would therefore be 20% versus 29.6%. Given a two-sided alpha error of 5%, a power of 80%, and a randomisation ratio of 2:1 (control group:experimental group), 466 couples receiving usual care (control group) and 233 couples in the experimental group are required. The total sample size was set to 750 couples (500 control group and 250 experimental group participants), allowing room for a 5% dropout rate.

A flowchart will be used to depict the total participants of each cohort, those per group, and those per gender. All eligible participants will be included in the analyses (since they belong to the global observational cohort), and groups—that is, the randomised control group versus experimental group, encompassing couples having accepted PEPCI and couples having refused PEPCI—will be compared according to the intention-to-treat principle. General and baseline characteristics will be compared between the groups.

An analysis of the primary objective (i.e., the effect of intervention on clinical pregnancy) will be performed with a logistic regression mixed model, with a fixed factor corresponding to the randomisation-arm intervention group and the centre being considered as a random factor. The intervention group will be considered as superior if the lower-limit 95% CI of the corresponding OR of pregnancy is greater than 1. In addition, as a non-negligible proportion of couples may refuse to receive the intervention being trialled, the intention-to-treat analysis may, therefore, dilute any treatment effects. Thus, we will use the statistical method complier average causal-effect analysis, which provides unbiased estimates of the treatment effect for patients who comply with the protocol. This will be considered as a secondary analysis.

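### The protocol's words on post-randomisation psychiatric diagnoses allow a one-arm exclusion that conflicts with its intention-to-treat comparison and must be reconciled with it

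*Protocol article*

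**What the plan says.** **Order of events.** Study recruitment describes what happens once a couple has agreed to biological sampling: "an ‘on-the-fly’ randomisation will be performed by the physician on a dedicated website that selects PEPCI candidate couples who are offered the PEPCI experimental intervention". Allocation therefore comes before the offer of PEPCI and before any programme assessment.

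**Who is examined.** Under Data collection and assays at baseline (M0): "For the members of couples who agreed to receive the intervention only, a detailed multidimensional evaluation will be performed". This evaluation includes the psychiatrist's structured diagnostic interview (MINI 5.0) of both partners. For everyone else, the baseline questionnaires for the whole cohort include the HAD scale, a self-reported screen.

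**What follows from a diagnosis.** Under Lifestyle interventions, in the item on psychological care and addiction: "In cases of a psychiatric diagnosis requiring specialised care, patients will be referred to a psychiatrist and not included in the study".

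**Eligibility.** Exclusion criterion 7 for the controlled trial covers "psychiatric pathologies requiring or currently under treatment". It applies to both arms.

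**Analysis.** The text under Fig. 1 sets all controls against all PEPCI candidates, whether or not they consented to the programme. Sample size and statistical analysis repeats this, with the experimental group "encompassing couples having accepted PEPCI and couples having refused PEPCI". Both places limit the comparison to eligible couples.

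**The concern.** A couple can reach the diagnostic interview only if it was randomised to the experimental arm and accepted PEPCI. An identical couple in the control arm, or one that refused, is never interviewed and stays in. If a diagnosis takes a couple out of the study, the two arms are no longer the groups that randomisation formed.

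The word eligible in the analysis text adds to the problem. Together with criterion 7, it lets an accepting experimental couple become ineligible on the strength of an interview that no control couple has.

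The primary comparison is at stake. If the removed couples conceive less often than average, the experimental arm looks better without any treatment effect. The arm also falls below its planned size.

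**Working it through.** **1. The plan's own sample size.** The inputs, all from Sample size and statistical analysis, are 20% in controls, 32% with PEPCI, 20% refusal, two-sided 5%, 80% power and 2:1 allocation.

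- Intention-to-treat rate: 0.80 × 0.32 + 0.20 × 0.20 = 0.296.
- Pooled rate: (2 × 0.20 + 0.296)/3 = 0.232.
- Controls: [1.96 √(0.232 × 0.768 × 3) + 0.8416 √(0.20 × 0.80 + 2 × 0.296 × 0.704)]² / 0.096² = 465.9, so 466 and 233.

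This matches the protocol. At 500/250 the power is 82.6% before dropout. No stated figure is wrong.

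**2. How much of the arm could be removed.** The protocol does not give a prevalence. Assume that a share *p* of individuals is diagnosed, independently between partners and independently of acceptance. Only acceptors (80%) are interviewed, so the removed share of the arm is *a* = 0.80 × [1 − (1 − *p*)²].

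| *p* | Accepting couples diagnosed | *a* | Couples removed of 250 | Arm left |
|---|---|---|---|---|
| 5% | 9.75% | 7.8% | 19.5 | about 231 |
| 10% | 19% | 15.2% | 38 | 212 |

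**3. Bias with no true effect.** Let *r* be the pregnancy rate in diagnosed couples, also assumed, with 20% overall. After removal, the experimental rate is (0.20 − *a r*)/(1 − *a*).

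- Smallest inflation: *a* = 0.078, *r* = 0.15 gives (0.20 − 0.0117)/0.922 = 20.4%, or +0.4 points.
- Largest inflation: *a* = 0.152, *r* = 0.05 gives (0.20 − 0.0076)/0.848 = 22.7%, or +2.7 points.
- Equal prognosis, *r* = 0.20: 20.0%, no bias.
- Better prognosis, *r* = 0.25: 19.6% and 19.1%, or −0.4 and −0.9 points.

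The planned intention-to-treat difference is 29.6 − 20 = 9.6 points.

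**4. Type I error.** This uses a pooled two-proportion z-test of 500 against the reduced arm, as an approximation to the planned mixed logistic model. In the largest case the pooled rate is (100 + 212 × 0.2269)/712 = 0.208. The standard error is 0.0333 pooled and 0.0339 unpooled. The rejection probability is Φ[(0.0269 − 1.96 × 0.0333)/0.0339] + Φ[(−0.0269 − 1.96 × 0.0333)/0.0339] = 0.129 + 0.003 = 13.2%. In the smallest case it is 5.3%.

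**5. If the couples are kept.** Assume that diagnosed couples do not receive PEPCI and conceive at 20%. With a share *q* of acceptors diagnosed, uptake is 0.80(1 − *q*) and the experimental rate is 0.20 + 0.12 × uptake.

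| *q* | Uptake | Rates | Power at 500/250 | Controls for 80% power |
|---|---|---|---|---|
| 0 | 80% | 20% vs 29.6% | 82.6% | 466 |
| 5% | 76% | 20% vs 29.1% | 79% | 514 |
| 10% | 72% | 20% vs 28.6% | 75% | 569 |

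**The case against.** **The sentence may mean only that the couple does not enter the programme.** It stands in a list of programme components and mentions neither the analysis set nor the end of follow-up. The analysis text points the other way, as do Experimental design and the Discussion, which keep all eligible people under observation in the cohort. This objection stands in part. A reader might infer that the trial will certainly drop these couples and that intention-to-treat is already broken, but the documents do not establish that. They contain two statements that cannot both be followed literally. Against the benign reading, the protocol says plainly that refusers receive usual care and remain in the comparison, whereas this sentence refers to the study itself.

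**Criterion 7 already filters both arms before randomisation.** It does, and only cases that it misses are at issue, so the true share may lie below the assumed range. But the instrument that finds the missed cases is used in one arm only, so the asymmetry remains.

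**The size is speculative.** Correct: prevalence and prognosis are both assumptions. It would also be an error to apply the 10–19% of couples to the whole arm, because refusers are never interviewed.

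**The sports physician's examination.** A reader might extend the point to contraindications found there. No part of the protocol says that couples are removed after that examination, so the point does not reach so far.

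**Conclusion.** The concern holds as a contradiction to be reconciled. As worded, the programme section allows a one-arm exclusion after randomisation, against the protocol's own intention-to-treat principle.

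If the words are followed as removal, the experimental rate under no effect shifts by about +0.4 to +2.7 points, two-sided type I error is about 5.3–13%, and the arm falls from 250 to about 212–231. These figures assume that 5–10% of individuals are diagnosed, that refusal is 20%, and that diagnosed couples conceive at 5–15% against 20% overall. The upper end needs diagnosed couples to conceive at a quarter of the average rate, for which the protocol gives no support. The structural fault does not depend on these figures, but the size and direction of the bias do.

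If the words mean only non-entry into the programme, there is no bias. What remains is non-uptake beyond the 20% refusal, which the sample size does not cover.

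**What to change.** Reconcile the sentence under Lifestyle interventions with the text under Fig. 1, exclusion criterion 7 and Sample size and statistical analysis. State that:

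- couples diagnosed after randomisation stay in their randomised arm, are followed to M12 and are analysed there whether or not they receive PEPCI;
- they count as non-uptake in the complier average causal-effect analysis;
- eligibility for the analysis is judged only on information available in both arms before randomisation.

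Referral itself is untouched; only membership of the study and of the analysis set changes.

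The change is one of wording, plus continued follow-up of these couples. Its cost is a more diluted intention-to-treat effect, so the planning figure should be restated. With the planned 500/250, power is about 79% if 5% of accepting couples do not receive PEPCI and about 75% if 10% do not, before dropout. Restoring 80% power would take 514 or 569 controls respectively, with half as many experimental couples (257 or 285).
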